### Intervention

2.6.

#### Intervention arm

2.6.1.

Participants in the intervention arm will receive the MyGeneMyDiet^®^ Recommendations. It is a gene-based nutrition and lifestyle recommendation developed by the research team by incorporating genetic information based on the result of a genetic test into the standard recommendations for weight management. The MyGeneMyDiet^®^ Recommendations are customized diet and lifestyle advice that will be based on the participant’s anthropometric data (BMI, waist circumference, body fat percentage), biochemical test results, dietary intake, physical activity level, and genetic risk profile.

Decision trees and coded messages were generated by simulating possible genotypes, anthropometric data, results of clinical tests, dietary intake, and physical activity level (Supplementary Table S1; Supplementary Figures S1–S4). A Scientific Advisory Board consisting of nutrition and dietetic professionals, genetic counselors, and a lifestyle medicine physician guided the team in developing the recommendations. The overview of the weight management recommendations among carriers of the risk alleles for *FTO* rs9939609, *UCP1* rs1800592, and *TCF7L2* rs7903146 is described in Table 1.

**Table 1 tab1:** Overview of the MyGeneMyDiet^®^ recommendations.

Outcomes	Genetic polymorphisms	Standard recommendations (control arm)	MyGeneMyDiet^®^ recommendations (Invervention arm)
Weight, BMI, and physical activity	*FTO* rs9939609	Achieve and maintain a normal BMI 20–40 min of daily moderate-intensity aerobic physical activity (32)	Achieve and maintain a normal BMI. 30–60 min of daily moderate-intensity aerobic physical (33)
Calorie requirement	*UCP1* rs1800592	Follow the recommended daily caloric intake based on desirable body weight (DBW) and physical activity level (PAL) (34)	Reduce 150 kcal from the recommended daily caloric intake (35)
Dietary fat intake	*TCF7L2* rs7903146	25–30% of the recommended caloric intake from fat (36)	15–20% of the recommended caloric intake from fat (18)

Should the participant in the intervention group have more than one genetic polymorphism, all the corresponding MyGeneMyDiet^®^ recommendations (based on the risk alleles they carry) will be given.

The intervention will be delivered by trained and registered nutritionist-dietitians who will meet with the participants during online counseling sessions in months 0, 3, 6, and 12. These sessions will track the compliance with the meal and exercise plan, and to adjust the caloric and weight loss goals of the participants.

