#### Inclusion criteria

2.3.1.

The trial targets overweight or obese individuals aged between 19 and 59, who indicate willingness to participate in the study. Their BMI should be equal to or greater than 25 but not more than 40 kg/m^2^. They should also have normal to pre-disease state level of fasting blood glucose, lipid profile, and blood pressure, and blood cortisol and thyroid hormone levels. They should carry at least one of the risk alleles of the three target genetic polymorphisms: A allele for *FTO* rs9939609, T allele for *TCF7L2* rs7903146, and G allele for *UCP1* rs1800592.

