### Sample size calculation

2.5.

To address the primary research question, at least 52 participants (*n* = 26 per group) are needed to detect a clinically meaningful difference of 5% weight loss after 6 months of intervention, assuming 80% power, an alpha of 5%, and a 0.25 SD in the main outcome variable (31). We aim to recruit 62 participants (*n* = 31 per group) to account for the potential dropout rate of 20%.

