### Statistical analysis plan

2.10.

Outcome data will be reported following the Consolidated Standard Reporting Trials (CONSORT) guidelines (46). An intention-to-treat analysis will be employed.

The mean and standard deviation (SD) will be used to report continuous variables while percentages will be used for categorical variables. Estimates of the different sources of attrition bias will be conducted using two-way analysis of variance (ANOVA) models. Student *t*-test will be used to compare the differences in means between the intervention and the control group for the primary and secondary outcome measures. One-way ANOVA will be used if the comparison of multiple subclasses is warranted, with Dunn’s multiple comparisons *post-hoc* test. Linear mixed models will be used to determine changes from baseline among the different study outcomes, with participant number retained as random effect. A two-sided alpha of 0.05 will be used for hypothesis testing.

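### Each gene-based component goes only to carriers of its allele, but dietary intake and physical activity are compared only between whole arms, which blurs each component's effect and adherence to it

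*Protocol article*

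**What the plan says.** All of this is in the protocol article.

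- **Who is eligible (2.3.1).** "They should carry at least one of the risk alleles of the three target genetic polymorphisms". One allele suffices, and the Discussion (section 3) confirms that participants may carry one or a combination.
- **Who receives what (2.6.1 and Table 1).** Table 1 pairs FTO with the activity advice, UCP1 with the calorie advice and TCF7L2 with the fat advice. The text below it says that a participant with several polymorphisms gets all the matching recommendations: these "based on the risk alleles they carry) will be given".
- **What controls receive (2.6.2).** Advice built on the same personal data, without the allele-based customisation.
- **Outcomes (2.7).** Weight, BMI, waist circumference and body fat percentage are primary. Dietary intake and physical activity, the behaviours that the components address, are secondary.
- **Adherence.** The Discussion paragraph of the abstract and section 2.1 make adherence to the advice a stated purpose, particularly in the inactive phase.
- **Analysis (2.10).** Student's t-test is to "compare the differences in means between the intervention and the control group for the primary and secondary outcome measures". Mixed models address change from baseline. One-way ANOVA is available if subclasses need comparing, but the subclasses are not named. Allele carriage appears nowhere in the section.

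**The concern.** For weight, the arms differ in a tailored package, and comparing whole arms tests that package. The behavioural outcomes are different, because each has its own component and that component reaches only part of the intervention arm. For the fat advice, an intervention participant without the TCF7L2 T allele appears to be in the same position as a control. The same holds for activity without FTO A and for the calorie reduction without UCP1 G.

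The arm mean of fat intake therefore mixes people asked to change it with people who were not. A small arm-wide difference could mean that carriers did not follow the advice, or that they followed it but were few. The stated comparison cannot separate these readings, although adherence is something the trial sets out to learn. A component that carriers take up well could be reported as having no effect.

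**Working it through.** **1. The plan's own figure.** Section 2.5 arrives at 26 evaluable people in each arm, 52 in all, for a 5% target at month 6. Its other inputs are given as "assuming 80% power, an alpha of 5%, and a 0.25 SD in the main outcome variable". Read literally, 0.05/0.25 is a standardised difference of 0.2, which needs 393 per arm. The 26 per group is not reproduced; it corresponds to a standardised difference of about 0.8. That is a separate matter. Below, d = 0.792, the value that gives 80% power with 26 per arm in a two-sided t-test at 0.05, serves only as a benchmark effect size. The plan states no power for any secondary outcome.

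**2. Dilution.** Let f be the share of the arm carrying the allele. The documents do not give it, so f is an assumption, taken from 0.25 to 0.9.

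Arm-wide difference = f × (effect in carriers) + (1 − f) × (effect in non-carriers).

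If non-carriers show no effect on the targeted outcome, this is f × (effect in carriers).

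**3. In the units of Table 1.** The fat ranges have midpoints of 17.5% and 27.5%, a prescribed gap of 10 percentage points. The calorie gap is 150 kcal. Suppose carriers follow the advice exactly and nothing else differs:

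| f | Arm-wide fat gap (10 × f) | Arm-wide calorie gap (150 × f) |
|---|---|---|
| 0.25 | 2.5 points | 37.5 kcal |
| 0.50 | 5 points | 75 kcal |
| 0.75 | 7.5 points | 112.5 kcal |
| 0.90 | 9 points | 135 kcal |

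At f = 0.5, full adherence by carriers gives the same arm-wide gap as half adherence would if everyone had been given the advice.

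**4. Power for an effect confined to carriers.**

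- Whole arms: standardised difference d × f with n = 26 per arm; noncentrality d × f × √(26/2).
- Carriers only: standardised difference d with n = 26f per arm; noncentrality d × √(26f/2).
- Ratio, carriers to whole arms: 1/√f.

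At f = 0.5 the whole-arm value is 0.792 × 0.5 × 3.606 = 1.43 and the carriers-only value is 0.792 × 2.550 = 2.02, a ratio of 1.41.

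| f | Whole arms | Carriers only |
|---|---|---|
| 0.25 | 11% | 26% |
| 0.50 | 29% | 49% |
| 0.75 | 56% | 67% |
| 0.90 | 71% | 76% |

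These figures ignore the extra variance from mixing carriers with non-carriers, which would lower the whole-arm values slightly (to 27% at 0.5 and 70% at 0.9). They also assume equal carrier numbers in the two arms, which is not assured because section 2.8 stratifies by BMI only.

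**5. Is the carrier comparison randomised?** Yes. Genotype is an eligibility criterion, so carriage is fixed before allocation and known in both arms. Carriers in one arm can be compared with carriers in the other without conditioning on anything that happens after randomisation.

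**The case against.** **The stated power.** A reader might infer that the 80% for weight is overstated because not everyone receives every component. The documents do not support this. Section 2.5 ties the 80% to a 5% weight-loss difference between the groups, which is already an average over whatever genotypes are enrolled. At that fixed difference, genotype mix takes nothing off the power. Every participant also carries at least one allele, so everyone in the intervention arm receives some gene-based component. A group with no expected effect on weight does not exist.

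**The question asked.** The Introduction asks about the recommendation as a whole against standard advice, and no objective is set for single components. This stands: whole-arm comparison is the right main test. It does not dispose of the adherence aim, which concerns the advice that each person was actually given.

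**Non-carriers may not be unaffected.** Table 1 is an overview, and the operative decision trees are in supplementary material not shown here. Fat advice could also change energy intake in people without UCP1 G. This stands as a caution. It weakens the dilution argument most for energy intake and less for fat intake and activity.

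**Subgroup detail belongs in an analysis plan.** Partly right; a fuller plan may contain such an analysis. But section 2.10 does fix the comparison for the secondary outcomes, and its provision for subclasses is conditional and does not mention genotype.

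**The gain is modest.** Carriers-only power stays below 80% at every share shown. That is why the added analysis should be labelled exploratory.

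**Conclusion.** The point holds for the secondary outcomes that a single component targets: fat intake, energy intake and physical activity. On these, the stated whole-arm comparisons average recipients of a component with people not given it. That dilutes its effect and obscures whether carriers followed the advice.

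The size depends on the carrier share, which the documents do not give, and on little or no effect in non-carriers. Under those assumptions the arm-wide difference shrinks in proportion to the share, and the carrier comparison is the more powerful at every share tried. The advantage is large at one half and small at nine tenths.

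The primary outcomes, their whole-arm analysis and the meaning of the 80% in section 2.5 are untouched. This is an inexpensive improvement to the secondary analysis and does not threaten the trial's main conclusion.

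**What to change.** Keep the whole-arm comparisons for weight and all other outcomes as the test of the tailored strategy. In section 2.10, add a prespecified comparison between arms, labelled exploratory, among carriers of the matching allele in both arms:

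- percent energy from fat in TCF7L2 T carriers;
- physical activity in FTO A carriers;
- energy intake in UCP1 G carriers, noting that the fat advice may also act on this outcome.

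A model with arm, carriage and arm-by-carriage terms that reports the effect in carriers is an equivalent form. Describe carriage of the three alleles by arm, so that readers can see the share each component reached and any imbalance.

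No change to section 2.5 is needed on this account. The cost is a few sentences and a few extra models, with no new data. The downside is fewer participants per comparison and additional exploratory tests, to be reported as estimates with confidence intervals.

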#### Control arm

2.6.2.

Participants in the control arm will be provided with the standard recommendations for weight management. For this study, the standard recommendations are based on the Philippines’ Nutrition Practice Guidelines (NPG) for the Screening and Management of Obesity, and other population-based recommendations including the 2012 Nutritional Guidelines for Filipinos (37), the *Pinggang Pinoy* (Filipino food plate model) dietary recommendations (38), and the WHO 2020 Guidelines on Physical Activity. Except for the customized recommendation based on alleles for *FTO* rs9939609, *UCP1* rs1800592, and *TCF7L2* rs7903146, the advice for the control arm will be based on the participant’s anthropometric data, biochemical test results, dietary intake, and physical activity level.

Participants in the control arm will also receive online nutrition counseling from trained and registered nutritionist-dietitians in months 0 (baseline), 3, 6, and 12. As part of the after-trial care, participants in the control arm will receive the corresponding MyGeneMyDiet^®^ Recommendation for Weight Management after the month 12 visit.

### Outcomes

2.7.

The primary outcomes will be the difference in weight, BMI, waist circumference, and body fat percentage between the arms after both the active and inactive phases. Secondary outcomes will include improvement in dietary intake, eating behavior, physical activity levels, glycated hemoglobin, and blood lipid profile. In addition, stages and motivation for weight loss and the knowledge and perceptions in nutrigenomics and genetic testing will be evaluated.

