**Methods and analysis:**

A parallel group, single-blind, randomized controlled trial will be conducted. Sixty-two overweight/obese individuals aged 19–59 years old will be recruited. Participants will be randomly allocated to either the intervention (*n* = 31) or the control arm (*n* = 31). Participants in the intervention group will receive the MyGeneMyDiet^®^ Recommendation for Weight Management, a gene-based nutrition and lifestyle recommendation that was developed based on existing evidence of the effects of *FTO* rs9939609 on body weight, BMI, and physical activity; *UCP1* rs1800592 on calorie intake; and *TCF7L2* rs7903146 on dietary fat intake. Participants in the control group will receive the standard recommendations for weight management. The primary outcomes will be the differences in weight, BMI, waist circumference, and body fat percentage between arms in both the active phase (6 months) and inactive phase (last 6 months) of the trial. Participants in both arms will be evaluated at baseline and in months 3, 6, 9, and 12.

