Earlier studies have shown that dietary advice based on genetic information resulted in specific changes in the intake of sodium and dietary fat (24, 25). However, substantial research showing the effectiveness of gene-based nutrition recommendations for improving weight and obesity-related outcomes are rather limited. Available evidence showed none or modest improvements in weight, lifestyle, and dietary behavior when advice was linked to genetic profiles (24, 26–28) or when genetic risks were disclosed to the participants (24, 25, 29, 30).

To expand the existing knowledge about the effects of gene-based nutrition and lifestyle recommendations, this randomized controlled trial aims to determine if the provision of the MyGeneMyDiet^®^ Recommendation for Weight Management and disclosure of genetic risk can help overweight/obese individuals achieve 5–10% weight loss in a 12-month trial when compared with the standard advice for weight management. Other primary outcomes include reduction in BMI, waist circumference, and body fat percentage.

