#### Anthropometric measurements

2.9.1.

Body weight and body fat percentage will be determined using a body composition analyzer (Tanita-MC78U, Tanita Corporation, Japan). Height will be measured using a stadiometer (Seca 217, Seca, Germany) while waist and hip circumference will be obtained using a non-stretchable tape measure (Seca 203, Seca, Germany). Anthropometric measurements will be done twice following a standard procedure. A third measurement will be taken if the difference between the two measurements is greater than 0.3 kg for weight, 0.5 cm for height, and 0.5 cm for waist circumference. The average of all the readings will be taken as the final estimated value of the measurement. BMI will be derived by dividing the weight in kilograms by height in meters squared. The percent body fat (BF%) will be assessed according to the chart by Gallagher et al. (39).

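### Four outcomes are primary after two phases, giving eight comparisons at an unadjusted 0.05, while the trial is sized on weight loss at 6 months alone

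*Protocol article*

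**What the plan says.** Section 2.7 (Outcomes) makes primary the "difference in weight, BMI, waist circumference, and body fat percentage between the arms after both the active and inactive phases". The abstract agrees: the same four measures are to be compared "between arms in both the active phase (6 months) and inactive phase (last 6 months) of the trial". Neither place ranks the outcomes or the phases.

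Section 2.10 (Statistical analysis plan) uses the Student t-test to "compare the differences in means between the intervention and the control group for the primary and secondary outcome measures", so primary and secondary outcomes are handled alike. It then states: "A two-sided alpha of 0.05 will be used for hypothesis testing". The one multiple-comparison procedure it names, Dunn's test, belongs to a different setting: "One-way ANOVA will be used if the comparison of multiple subclasses is warranted". It does not reach the eight primary comparisons.

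Section 2.5 (Sample size calculation) is narrower. It ties the primary research question to a "clinically meaningful difference of 5% weight loss after 6 months of intervention" and refers to one main outcome variable. Section 1 (Introduction) asks whether the intervention helps participants "achieve 5–10% weight loss in a 12-month trial when compared with the standard advice for weight management" and then lists BMI, waist circumference and body fat percentage as further primary outcomes.

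Section 2.9.1 says how BMI is obtained: "BMI will be derived by dividing the weight in kilograms by height in meters squared".

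**The concern.** Four outcomes after two phases make eight primary comparisons. As written, each is tested at the full 0.05, and only one of them, weight at 6 months, has a sample size behind it. If weight loss differs at month 6 but not at month 12, or waist circumference differs and weight does not, the protocol gives no basis for saying whether the trial met its primary objective. With eight chances available, the overall false-positive rate can be well above the stated 5%.

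BMI adds a second problem. With one height per adult participant, percent change in BMI equals percent change in weight. Significant results on both would look like two confirmations but carry the information of one.

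**Working it through.** **The plan's own figures.** The protocol states no overall error rate, so there is none to reproduce. Its sample size is 26 per group at 80% power and two-sided 5%. By the normal approximation, 26 per group corresponds to a standardised effect of (1.960 + 0.842) × √(2/26) = 0.777; the exact t-test gives 0.792. Section 2.5's own inputs do not lead there: a difference of 0.05 with SD 0.25 needs 2 × (1.960 + 0.842)² × (0.25/0.05)² ≈ 393 per arm. That is a separate matter and does not affect the count of tests or the error rates below.

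**Number of comparisons.** 4 outcomes × 2 phases = 8 (section 2.7 and abstract).

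**BMI against weight.** For fixed height h, (w₁/h²)/(w₀/h²) = w₁/w₀, so the percent changes are identical. In absolute units the two differ only through variation in height between people. This is why a correlation of 0.95–0.98 is assumed below.

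**Ceiling, from stated inputs only.** With eight independent tests at 0.05:
- either direction: 1 − 0.95⁸ = 0.337
- favouring the intervention: 1 − 0.975⁸ = 0.183

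The outcomes are positively correlated, so the true rates are lower.

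**With correlation (assumed; the documents give none).** Eight correlated normal test statistics were simulated under no treatment effect, 400,000 draws per scenario. The event counted is at least one two-sided p < 0.05, first in either direction and then only in favour of the intervention. Weight and BMI are given the same correlations with waist and with body fat.

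| Weight–BMI | Weight–waist / weight–fat / waist–fat | Between phases | Either direction | Favouring intervention |
|---|---|---|---|---|
| 0.98 | 0.8 / 0.8 / 0.7 | 0.95 | 13.5% | 6.8% |
| 0.98 | 0.8 / 0.8 / 0.7 | 0.8 | 16.1% | 8.0% |
| 0.97 | 0.7 / 0.6 / 0.5 | 0.7 | 20.1% | 10.0% |
| 0.95 | 0.6 / 0.5 / 0.4 | 0.7 | 21.8% | 11.0% |
| 0.95 | 0.4 / 0.3 / 0.3 | 0.5 | 25.5% | 12.9% |

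The range is therefore about 14–26% in either direction and 7–13% in favour of the intervention. One test gives 5% and 2.5%. As a wider check, setting every pair of outcomes to a common correlation between 0.3 and 0.9 gives 12–30% and 6–15%.

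**Cost of adjusting instead of choosing.** Bonferroni over eight tests uses 0.05/8 = 0.00625 each, critical value 2.734.
- At an assumed standardised effect of 0.777 and 26 per arm, power is Φ(2.802 − 2.734) ≈ 0.53, down from 0.80.
- At an assumed 0.80, with t-tests, power is 0.52, down from 0.81.
- Restoring 80% at 0.777 takes 2 × (2.734 + 0.842)²/0.777² ≈ 43 per arm.

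These effect sizes are assumptions; neither is stated in the protocol.

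**The case against.** Several points on the other side have force.

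- **A lead outcome is indicated.** Section 2.5 links the primary research question to weight loss at 6 months, and section 1 puts weight loss first. This stands, and it makes the fix easy. It is still not a hierarchy: section 2.7 and the abstract, where the outcomes are defined, do not carry it.
- **Six versus 12 months.** A reader might infer that section 1 fixes the endpoint at month 12 and so flatly contradicts section 2.5. The text does not support that. Its reference to 12 months can describe the trial's length, and both phases are expressly primary. What remains is inconsistency about which time point leads.
- **Success rule.** A reader might infer that any one of eight significant results is declared a success. The protocol does not say so, and a separate analysis plan or full protocol, not shown here, could add a hierarchy or an adjustment. This limits the error rates to a conditional statement. It does not remove the point, because the multiple primary designation, the unqualified 0.05 and the narrower sample-size basis are all written in this document.
- **Pilot status.** The title calls the trial a pilot. The same title says it evaluates effectiveness, and section 2.5 claims 80% power, so the label does not dispose of the issue.
- **Bonferroni is harsh** when tests are highly correlated. Agreed; it is shown only as a comparator.

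**Conclusion.** The point holds. The protocol designates eight primary comparisons, one pair nearly duplicated at each phase, under one unadjusted 0.05, and powers only weight loss at 6 months. If any one were read as success, the chance of at least one false-positive primary result is about 14–26%. That rests on assumed correlations (weight–BMI 0.95–0.98, other pairs 0.3–0.8, between phases 0.5–0.95). Only the 34% ceiling follows from stated inputs, and it requires an independence that cannot hold here.

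It is tempting to read the 14–26% as the chance of wrongly calling the intervention effective. It is not: it includes significant results favouring control. The chance of a false result in favour of the intervention is about 7–13%, roughly three to five times the 2.5% of a single test.

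**What to change.** Name one primary outcome and time point that match section 2.5: percent change in weight from baseline to month 6. Make weight change at month 12, waist circumference and body fat percentage secondary outcomes, tested at 0.05 in a prespecified fixed order that stops at the first non-significant result. The order is for the sponsor to choose. Treat BMI as supportive because it repeats weight. Align the abstract and sections 1, 2.5 and 2.7 before any unblinded analysis.

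The cost is a protocol amendment, which section 4.1 says needs ethics committee approval first. Three outcomes and the 12-month comparison lose the primary label, and under fixed-order testing a later outcome cannot be claimed once an earlier one fails. No participants are added and the primary test keeps the full 0.05. Keeping all eight as primary under Bonferroni would instead leave power near 50% at the planned size.
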